## 3.4 Treatments

### 3.4.1 Investigational products

(a) Lapatinib

GlaxoSmithKline will supply Lapatinib to the investigator for use

#### Descriptive information for Lapatinib can be found in the Investigator’s Brochure

####

#### 3.4.1.1 Doses and treatment regimens

1. Lapatinib

Lapatinib is supplied as 250 mg oval, biconvex, orange film-coated tablets. The lapatinib dose level for this study is 1500 mg. The tablets are packaged into HDPE bottles with child-resistant closures. Study treatment will be dispensed to subjects on Day 1 and every monthly visit thereafter until the subject withdraws, or completes the study.

**Route of administration**

Lapatinib treatment will be taken orally once a day, every day about the same time. Patients should be advised to take lapatinib on an empty stomach (either 1 hour before or 1 hour after meals). If the subject forgets to take a dose, they should take the last missed dose as soon as they remember, as long as it is at least 12 hours before the next dose is due.

#### Guideline for dispersing whole lapatinib tablets

The following procedure is recommended for administering dispersed whole tablet(s) to patients who are unable to swallow:

Place ½ cup (120mL) of water in a glass container, then add six 250 mg lapatinib tablets to the container. Cover the container, let it stand for 5 minutes, and then stir the mixture intermittently for 10-20 minutes or until it is fully dispersed. Stir the container for 5 seconds then administer. Rinse the container with a ¼ cup (60mL) aliquot of water and administer (total of ¾ cup, 180mL of liquid is dispensed).

1. Lapatinib dose interruption/reduction

See section 3.5 - Management of Toxicity

####

#### 3.4.1.2 Storage

The intact bottles should be stored at controlled room temperature (15°C-30°C).

#### 3.4.1.3 Accountability

- Deliveries of such products from GlaxoSmithKline are correctly received by a responsible person (e.g., a pharmacist)
- Deliveries are recorded
- Study treatments are handled and stored safely and properly
- Study treatments are dispensed only to study subjects in accordance with the protocol
- Subjects must return all unused medication and empty containers to the investigator

At the end of the study, it must be possible to reconcile delivery records with records of usage and destroyed/returned stock. Any discrepancies must be accounted for. Certificates of delivery and return must be signed, preferably by the investigator or a pharmacist.

The principal investigator/sub-investigator must request the subject to return unused drugs which may be left over for subject’s negligence or any other reasons, as well as empty cartons and packaging

### 3.4.2 Pre-study, concomitant and post-study treatment(s)

#### 3.4.2.1 Treatment for cancer

Except for lapatinib, no systemic treatment or radiotherapy known to have an effect on breast cancer may be used during the study.

####

#### 3.4.2.2 Lapatinib Prohibited Medication List

Gastric pH Modifiers. GSK is no longer prohibiting gastric pH modifiers (i.e. H2 blockers and PPIs). This is based on collection of concurrent med use and the observation that PK was no different between pts on gastric pH modifiers and those not taking gastric pH modifiers.

Lapatinib is a substrate for CYP3A4. Inducers and inhibitors of CYP3A4 may alter the metabolism of lapatinib. The following list of CYP3A4 inducers and inhibitors are prohibited from screening through discontinuation from study.

| **Drug Class** | **Agent** | **Wash-out1** |
| --- | --- | --- |
| **CYP3A4 Inducers** | | |
| Antibiotics | all rifamycin class agents (e.g., rifampicin, rifabutin, rifapentine) | 14 days |
| Anticonvulsants | phenytoin, carbamezepine, barbiturates (e.g., phenobarbital) |
| Antiretrovirals | efavirenz, nevirapine |
| Glucocorticoids (oral) | cortisone (>50 mg), hydrocortisone (>40 mg), prednisone (>10 mg), methylprednisolone (>8 mg), dexamethasone (>1.5 mg)2 |  |
| Other | St. John’s Wort, modafinil |  |
| **CYP3A4 Inhibitors** | | |
| Antibiotics | clarithromycin, erythromycin, troleandomycin | 7 days |
| Antifungals | itraconazole, ketoconazole, fluconazole (>150 mg daily), voriconazole |
| Antiretrovirals, Protease Inhibitors | delaviridine, nelfinavir, amprenavir, ritonavir, indinavir, saquinavir, lopinavir |
| Calcium channel blockers | verapamil, diltiazem |
| Antidepressants | nefazodone, fluvoxamine |
| GI Agents | cimetidine, aprepitant |
| Other | grapefruit, grapefruit juice |
| amiodarone | 6 months |
| **Miscellaneous** | | |
| Antacids | Mylanta, Maalox, Tums, Rennies | Excluded 1 hour before and after dosing |
| Herbal or dietary supplements | ginkgo biloba, kava, grape seed, valerian, ginseng, echinacea, evening primrose oil, and St John's Wort | 14 days |
| 1. At the time of screening, if a patient is receiving any of the above listed medications/substances, the medication or substance must be discontinued (if clinically appropriate) for the period of time specified prior to administration of the first dose of lapatinib and throughout the study period in order for the patient to be eligible to participate in the study. 2. Glucocorticoid daily doses (oral)  1.5 mg dexamethasone (or equivalent) are allowed. Glucocorticoid conversions are provided in parentheses. | | |

## 3.5 Management of Toxicity

**3.5.1 Criteria for Evaluating Cardiac and Respiratory Events**

**3.5.1.1 Asymptomatic Events**

Subjects who have a ≥ 20% decrease in left ventricular cardiac ejection fraction (LVEF) relative to baseline, and the LVEF is below the institution's lower limit of normal, should have a repeat evaluation of ejection fraction 1-2 weeks later while still receiving investigational product.

If the repeat ejection fraction evaluation confirms a ≥ 20% decrease in LVEF relative to baseline, and the ejection fraction is below the institution's lower limit of normal, then investigational product should be temporarily discontinued.

If the LVEF recovers during the next 3 weeks, after consultation and approval by the GSK Medical Monitor, the subject may be restarted on study treatment at a reduced dose. For such subjects, monitoring of LVEF will then be performed 2 weeks and 4 weeks after re-challenge, and then every 4 weeks thereafter.

If repeat ejection fraction evaluation still shows a decrease ≥ 20% in LVEF relative to baseline and the value is below the institution's lower limit of normal, then the subject should be withdrawn from investigational product. Ejection fraction should continue to be monitored every 4 weeks for at least 16 weeks or until resolution.

**3.5.1.2 Symptomatic cardiac events**

**Subjects with an NCI CTCAE Grade 3 or 4 left ventricular systolic dysfunction or interstitial pneumonitis must be withdrawn from therapy.**

Note: Copies of echocardiograms and/or MUGA scans performed on subjects who experience a ≥ 20% decrease in LVEF relative to baseline (asymptomatic or symptomatic), and a cardiac ejection fraction is below the institution's lower limit of normal, will be required by GSK for review by an independent board. A ≥ 20% relative decrease from baseline in LVEF (asymptomatic or symptomatic), that is below the institution’s lower limit of normal is considered an SAE and must be reported to GSK.

**3.5.2 Rash**

Skin rash (usually grade 1-2) has been observed during the first several days of treatment with EGFR inhibitors and has been observed to diminish in severity after 4 weeks of treatment in many patients. In some patients, this rash appeared to be treatable with standard acne therapies, including topical and oral antibiotics used to treat acne. Anecdotal reports of improvement have occurred with several agents. In patients with severe rash, treatment may need to be discontinued or the dose reduced. Anecdotal reports of improvement have occurred with any of the following: minocycline, topical tetracycline, topical clindamycin, topical silver sulfadiazine, diphenhydramine, oral prednisone (short course).

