**1.3.4 Clinical Pharmacokinetics**

The pharmacokinetics of lapatinib are similar in healthy volunteers and patients, demonstrating oral absorption that is incomplete, highly variable, and sometimes delayed. After dosing, plasma concentrations rise to a peak at approximately 4 h and thereafter decline with measured half-lives averaging up to 14 h. However, accumulation with daily dosing achieves steady state in 6-7 days, which suggests a true elimination half-life on the order of 24 h. Administration of the same daily dose in a BD schedule results in 2‑fold greater systemic exposure than a OD schedule. Despite this inconsistency, systemic exposure generally increases with increasing dose. Absorption is increased by ingestion with food. Elimination of lapatinib is predominantly through metabolism by CYP3A4/5 with negligible renal excretion. Significant changes in systemic exposure to lapatinib result from co-administration of drugs that are potent inhibitors or inducers of CYP3A.

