**3.5.4 Nausea**

Routine premedication for nausea is not necessary, but symptomatic patients should be treated with standard antinausea/antiemetic therapy as necessary.

If the patient vomits after taking the tablets, the dose is replaced only if the tablets can actually be seen and counted.

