**Table 6. Lapatinib Starting Dose and Dose Reduction Schedule**

| Starting dose | 1500 mg/day | *** Patients requiring a third dose reduction should be taken off study unless in the opinion of the investigator & GSK Medical Monitor, there is reason to believe that the patient is still experiencing clinical benefit |
| --- | --- | --- |
| First dose reduction | 1250 mg/day |

* if no recovery after 3 weeks of holding drug, patients should go off study unless in the opinion of the investigator & GSK Medical Monitor, there is reason to believe that the

patient is still experiencing clinical benefit.

**Table 7**. Dose Reduction Criteria and Guidelines for Management of lapatinib Associated Toxicity

|  | Grade | **Guideline for management** | **lapatinib dosage modification*** |
| --- | --- | --- | --- |
| Diarrhea | 1 | No intervention | None |
| 2 | Loperamide (4 mg at first onset,  followed by 2 mg every 2–4 hrs  until diarrhea free for 12 hrs) | None; If unacceptable to patient or medically concerning then hold until recovery  to < grade 1, up to 21 days*. Restart at same dose**. |
| > 3 (*despite optimal*  *use of loperamide)* | Hold until recovery to < grade 1, up to 21 days*. And then reduce 1 dose level. |
| Rash | 1 | No intervention | None |
| 2 | Any of the following:  minocycline+, topical  tetracycline or clindamycin,  topical silver sulfadiazine,  diphenhydramine,  oral prednisone (short course) | None; If unacceptable to patient or medically concerning then hold until recovery  to < grade 1, up to 21 days*. Restart at same dose**. |
| > 3 | Hold until recovery to < grade 1, up to 21 days*. And then reduce 1 dose level. |
| Other  Toxicity **(excluding**  **left ventricular**  **dysfunction and**  **pneumonitis,**  **see below)** | 1 | No Intervention | None |
| 2 | Treatment as appropriate | None; If unacceptable to patient or medically concerning then hold until  recovery to < grade 1, up to 21 days*. Restart at same dose **. |
| 2 prolonged or  clinically significant  and grade > 3 | Treatment as appropriate | Hold until recovery to < grade 1, up to 21 days and then reduce 1 dose level* |

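### The rash guidance lists oral prednisone without a dose limit although the prohibited-medication list bans it above 10 mg, and that list's H2-blocker sentence conflicts with its own cimetidine entry

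*Protocol*

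**What the plan says.** **Rash.** Section 3.5.2 ends with agents for which improvement has been reported anecdotally, among them "topical silver sulfadiazine, diphenhydramine, oral prednisone (short course"). Table 7 lists "oral prednisone (short course") in its management column for grade 2 rash. In the same row lapatinib continues unchanged unless the rash is unacceptable to the patient or medically concerning.

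**Prohibited drugs.** Section 3.4.2.2 states: "The following list of CYP3A4 inducers and inhibitors are prohibited from screening through discontinuation from study". Its oral glucocorticoid row, under CYP3A4 inducers, includes "hydrocortisone (>40 mg), prednisone (>10 mg), methylprednisolone (>8 mg"). Footnote 1 to that table requires listed agents to be stopped before the first dose and for the whole study period. Footnote 2 permits low daily oral glucocorticoid doses, expressed as a dexamethasone equivalent.

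**Gastric acid.** The same section opens with "GSK is no longer prohibiting gastric pH modifiers (i.e. H2 blockers and PPIs"). The table below it lists cimetidine among the CYP3A4 inhibitors.

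**Eligibility.** Exclusion criterion 8 (section 3.3.2) excludes patients who need a CYP3A4 inducer or inhibitor and sets no dose threshold.

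**Exposure.** Section 1.3.4 states: "Significant changes in systemic exposure to lapatinib result from co-administration of drugs that are potent inhibitors or inducers of CYP3A".

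**The concern.** An investigator treating a rash will look at section 3.5.2 and Table 7. Nothing there says that one listed option is restricted elsewhere. A site can follow one instruction in good faith and break another.

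The ban exists to protect lapatinib exposure. The trial has 20 patients, no control arm and CTC counts as its primary outcome, and two consecutive CTC increases end treatment. Section 3.5.2 places rash in the first days of treatment, easing after four weeks in many patients. The first on-treatment CTC sample is at week 4, so rash treatment may fall in the interval that this sample covers. Whether a drug in that interval was permitted, prohibited or an accepted exception should not depend on which section the site happened to read.

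**Working it through.** The check is mainly a comparison of texts. The protocol has no figure of its own on this point to reproduce.

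**1. Prednisone**

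| | Table 7 and 3.5.2 | 3.4.2.2 |
|---|---|---|
| Status of oral prednisone | listed for rash | banned above 10 mg |
| Dose limit | none | 10 mg |
| Period | during treatment | screening to discontinuation |
| Exception for toxicity | not mentioned | none |
| Reference to the other text | none | none |

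The overlap is conditional. A course at or below the threshold satisfies both texts; a course above it satisfies Table 7 and breaches 3.4.2.2. Doses were given in Table 7 where thought necessary: its footnote sets one for minocycline. Because lapatinib normally continues in the grade 2 row, giving prednisone alongside lapatinib is a foreseen situation.

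**2. Exclusion criterion 8**

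The criterion has no dose threshold, whereas 3.4.2.2 allows low-dose oral glucocorticoids. The two texts therefore draw the line for the same drug class differently.

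**3. H2 blockers**

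The opening sentence of 3.4.2.2 lifts the restriction on the class. The table restricts cimetidine at any dose. The table calls it only a GI agent; that it is an H2 blocker is general pharmacology. No dose condition separates the two statements.

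**4. Scale**

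- Input: drug-related rash at 1500 mg once daily, 89/273 (Table 3, all grades).
- Input: planned sample size, 20 (synopsis and section 3.1).
- Rate: 89/273 = 0.326.
- Expected patients with related rash: 20 × 0.326 = 6.5, or about 6 to 7.

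This bounds from above the expected number reaching the prednisone option. Table 7 prescribes no intervention for grade 1, section 3.5.2 describes rash as usually grade 1–2, and Table 3 has no split by grade. Prednisone is also only one of several listed agents. The expected number given a prohibited dose therefore lies somewhere between 0 and about 6.5 of 20. Each patient is 1/20 = 5 percentage points of the sample.

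**5. What cannot be calculated**

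The protocol gives no uptake of prednisone, no dose for the short course and no exposure change for such a course. Section 1.3.4 attaches significant changes to potent agents, and section 3.4.2.2 says only that metabolism may be altered.

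**The case against.** The strongest reply is that a study-wide ban and a list of options are normally read together. Prednisone within the limit complies with both, so this is a missing cross-reference. Section 3.5.2 reports anecdote and recommends nothing firmly. Cimetidine is banned as a CYP3A4 inhibitor, while the opening sentence concerns gastric pH, so a specific entry could coexist with the class statement. Table 5 already records concurrent medication at the on-treatment CTC visits, so a course would be documented.

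Much of this stands. The prednisone conflict depends on dose, Table 7 carries more weight than 3.5.2, and the cimetidine point does not concern management of a listed lapatinib toxicity. But the protocol nowhere says that the prohibited list governs the toxicity guidance, and the H2-blocker sentence makes no exception. Recording a drug does not settle whether it was allowed.

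A reader might go further and infer that two other texts contradict the list: "including topical and oral antibiotics used to treat acne" in 3.5.2 and "symptomatic patients should be treated with standard antinausea/antiemetic therapy as necessary" in 3.5.4. They do not. The antibiotics that 3.5.2 and Table 7 name are not on the list, and 3.5.4 names no drug. Both can be followed with permitted agents.

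**Conclusion.** The point holds in limited form. There are two conflicts in operative text: prednisone without a dose limit in Table 7 (echoed in 3.5.2) against the ban above 10 mg, and H2 blockers declared permitted against cimetidine prohibited. Exclusion criterion 8 adds a mismatch in threshold.

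On size, about 6 to 7 of 20 patients is an upper bound on the expected number reaching the rash guidance. It assumes that the Table 3 rate carries over to this trial.

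Three stronger conclusions are tempting and are not supported:

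- That a site would give a prohibited drug. It could, if it chose prednisone and exceeded the threshold.
- That CTC results are thereby confounded. Neither the exposure change nor its effect on counts is given, and for more severe or unacceptable rash Table 7 holds lapatinib, so part of a course may fall off drug.
- That patients would be withdrawn for it. Section 3.3.3.1 requires severe non-compliance in the investigator's judgement.

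**What to change.** Reconcile Table 7 and section 3.5.2 with section 3.4.2.2 and exclusion criterion 8. Two routes are open: cross-refer the rash options to the prohibited list, or state in 3.4.2.2 that an exception for toxicity management exists and how such use is recorded against the CTC samples. Bring the H2-blocker sentence and the cimetidine entry into agreement. Which text stands is for the sponsor to decide.

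A pointer to 3.4.2.2 from section 3.5.4 and from the acne-antibiotic phrase in 3.5.2 would be a useful optional clarification.

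The cost is a wording amendment to a few short passages, with no new procedures or visits. If the prohibition is kept as it is, the rash options become somewhat narrower.

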**3.5.3** **Diarrhea**

Diarrhea has been seen with lapatinib and with other EGFR inhibitors. In general EGFR inhibitor-induced diarrhea has been transient, usually not of sufficient severity to hinder administration of the agents, and responsive to loperamide. The recommended dose of loperamide is 4 mg at first onset, followed by 2 mg q 2–4 hr until diarrhea free for 12 hr.

**Lapatinib Diarrhea Management Guidelines:**

1. Uncomplicated grade 1-2 diarrhea:
   - Stop all lactose containing products;
   - Drink 8-10 large glasses of clear liquids a day;
   - Eat frequent small meals;
   - Grade 2 diarrhea hold cytotoxic chemotherapy;
   - Grade 2 diarrhea consider dose reduction of lapatinib (discuss with medical monitor);
   - Administer standard dose of loperamide:
     - Initial dose 4mg followed by 2mg every 4 hours or after every unformed stool.
     - We suggest continuation of loperamide until diarrhea free for 12 hours.
2. For grade 3 or 4 diarrhea or grade 1 or 2 with complicating features (severe cramping, severe nausea/vomiting, decreased performance status, fever, sepsis, grade 3 or 4 neutropenia, frank bleeding, dehydration):
   - Use intravenous fluids as appropriate, consider hospital admission;
   - Use prophylactic antibiotics as needed (example fluoroquinolones), especially if diarrhea is persistent beyond 24 hours or there is fever or grade 3-4 neutropenia;
   - Hold both cytotoxic chemotherapy and lapatinib and discuss with medical monitor.

These broad general management principles are recommended to proactively try and avoid more serious complications by active management of the diarrhea syndrome. Guidelines such as these should never replace sound clinical judgment. Our experience thus far suggests that when lapatinib is used as monotherapy we mostly are dealing with uncomplicated grade 1 or 2 diarrheas. These general management principles do not discuss comprehensive management of more serious or protracted diarrhea syndromes.

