**3.6 Dosing delays/dose modifications**

Starting dose and dose modifications for unacceptable toxicity are listed in Table 6. For toxicity that is thought to be related to lapatinib, the daily dose of lapatinib will be decreased according to the schedule displayed in the Table 7.

Dose adjustments are to be made according to the greatest degree of toxicity. Toxicities will be graded using NCI Common Terminology Criteria for Adverse Events (CTCAE) version 3.0.

The most common toxic effects of lapatinib are:

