**Gastrointestinal Disorders:**

Diarrhea which may lead to dehydration; nausea, and vomiting.

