**3.6.1 Dose Delays and Dose Reductions**

Treatment may be delayed, up to 2 weeks, to allow for resolution of toxicity except in the event of NCI CTCAE Grade 3 or 4 left ventricular cardiac dysfunction or NCI CTCAE Grade 3 or 4 interstitial pneumonitis. The Investigator must consult the GSK Medical Monitor prior to continuing therapy for any subject requiring a delay of more than 2 weeks for unresolved toxicity, but in general, such subjects should be withdrawn from the study. If treatment is delayed for reasons other than toxicity (i.e., unplanned travel or vacation, or lack of transportation to the site) and the subject has insufficient investigational product available, the subject should resume the usual dosing schedule once drug supply has been made available. However, if the subject has been off therapy for more than 2 weeks, the Investigator must consult the GSK Medical Monitor prior to continuing therapy.

Dose reduction for drug-related toxicity is permitted; however the GSK Medical Monitor must be consulted prior to implementing any change in dosing. Only one dose reduction is permitted per subject and subjects should not be rechallenged to a higher dose level. If a NCI CTCAE Grade 3 or 4 drug-related event (other than left ventricular cardiac dysfunction or interstitial pneumonitis) has occurred, the investigator may discuss with the GSK Medical Monitor whether a reduction of dose is appropriate.

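### Grade 1 diarrhoea with complicating features: section 3.5.3 holds lapatinib, but Table 7's Grade 1 row leaves the dose unchanged and does not point back

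*Protocol*

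**What the plan says.** Section 3.5.3 (Lapatinib Diarrhea Management Guidelines) has two tiers.

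- Uncomplicated Grade 1-2: dietary measures, oral fluids and loperamide ("Administer standard dose of loperamide"), with loperamide not confined to Grade 2. At Grade 2 the site is also asked to consider lowering the lapatinib dose after talking to the medical monitor.
- The second tier applies "For grade 3 or 4 diarrhea or grade 1 or 2 with complicating features". The listed features include dehydration, fever, worsened performance status, sepsis, bleeding and Grade 3-4 neutropenia. The instruction is "Hold both cytotoxic chemotherapy and lapatinib and discuss with medical monitor".

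Table 7 (section 3.6.1) is organised by grade. Its first diarrhoea row reads "Diarrhea | 1 | No intervention | None". Loperamide and a conditional hold appear only from Grade 2.

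Three other places bear on which text governs. The end of section 3.4.1.1 refers dose interruption and reduction onward: "See section 3.5 - Management of Toxicity". Section 3.6 says that, for toxicity thought related to lapatinib, "the daily dose of lapatinib will be decreased according to the schedule displayed in the Table 7". Section 3.6.1 adds that "the GSK Medical Monitor must be consulted prior to implementing any change in dosing".

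**The concern.** The two places answer one bedside question differently: does a patient with Grade 1 diarrhoea and, say, mild dehydration keep taking lapatinib? Section 3.5.3 says hold. Table 7, read alone, says change nothing. Table 7 is the compact by-grade reference that a site is likely to consult, and nothing in it warns that a stricter rule sits elsewhere.

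The event is a common one. Diarrhoea is the most frequent drug-related event in Table 3, and section 3.6 itself links it to the complication at issue: "Diarrhea which may lead to dehydration; nausea, and vomiting". What is at stake is patient safety and consistent handling across patients, not an analysis.

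**Working it through.** The Protocol states no figure on this point, so the check is mainly a comparison of texts.

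**Step 1. Compare by presentation.**

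| Presentation | Section 3.5.3 | Table 7, diarrhoea block | Agreement |
|---|---|---|---|
| Grade 1, uncomplicated | Diet, fluids, loperamide; dose unchanged | No supportive measure; dose unchanged | Dosing agrees; supportive care does not |
| Grade 1 with a complicating feature | Hold; discuss with monitor | Dose unchanged, no exception | Conflict |
| Grade 2, uncomplicated | Diet, fluids, loperamide; consider lowering the dose | Loperamide; dose unchanged, or a conditional hold and restart at the same dose. Reduction only if Grade 2 recurs after an earlier hold or the patient cannot accept it | Partial |
| Grade 2 with a complicating feature | Hold; discuss with monitor | Hold allowed if medically concerning | Broadly compatible |
| Grade 3 or higher | Hold; discuss with monitor | Hold, then reduce one level | Agree on the hold |

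The dosing conflict is therefore confined to the second row.

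**Step 2. Ask which complicating features another Table 7 row would catch.** Section 3.6 bases dose adjustment on the worst-graded toxicity, so a complicating feature may be held in its own right under Other Toxicity:

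- Related to lapatinib and Grade 3 or higher: hold.
- Related, Grade 2, prolonged or clinically significant: hold.
- Related, other Grade 2: hold at discretion.
- Related, Grade 1: no change.
- Thought unrelated to lapatinib: outside Table 7, because section 3.6 limits it to related toxicity.

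What remains is Grade 1 diarrhoea with a feature that is itself low-grade or judged unrelated. Section 3.5.3 would hold lapatinib there; Table 7 would not.

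**Step 3. Look for a rule of precedence.** Section 3.4.1.1 points to section 3.5 for interruptions. Section 3.6 points to Table 7 for decreases, but Table 7 also prescribes holds, so both texts cover holds. Table 7's footnotes deal with failure to recover after 3 weeks, recurrent or unacceptable Grade 2 symptoms, and the minocycline dose. None mentions complicating features or section 3.5.3. The section 3.6.1 consultation rule is triggered by a change in dosing, so a reader of a no-change row has no prompt to call.

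**Step 4. Size.** Inputs: 147 of 273 patients at 1500 mg had related diarrhoea of any grade (Table 3), and 20 patients are planned.

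- 147/273 = 0.538, and 0.538 x 20 = 10.8 patients, assuming the earlier rate carries over.
- Affected patients = 10.8 x p, where p is the share of these with Grade 1 diarrhoea and an uncovered feature. The Protocol gives nothing from which p can be obtained. The 10.8 is thus a ceiling under that assumption, not an estimate.
- Dehydration accounts for 49 of 1729 SAE reports (2.8%), of which 21 (43%) were called drug related (section 1.3.3.2.1). This is a share of serious reports across the whole lapatinib programme and says nothing about p.

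**The case against.** The strongest reply is that there is no contradiction, only a general rule and a specific exception. Section 3.4.1.1 sends interruptions to section 3.5, a hold is an interruption, and section 3.5.3 is explicit. Table 7 does not tell the site to disregard it. Section 3.5.3 also describes its advice as general principles subject to clinical judgment, and says that diarrhoea on monotherapy is mostly uncomplicated Grade 1 or 2.

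Much of this stands. Reading section 3.5.3 as the exception is natural, and Step 2 shows that Table 7 already holds the more severe related features. But the reading works only for someone with both texts open, since Table 7 carries holds of its own and no pointer. Clinical judgment may soften the mismatch but does not make the instructions agree.

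There are also signs that the two texts were not reconciled. Section 3.5.3 tells sites to hold cytotoxic chemotherapy, although section 3.4.2.1 bars other systemic anticancer treatment, and the Grade 2 advice differs as well. That favours an oversight over a deliberate structure, though this is an inference.

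It is also fair to say that the supportive-care difference at Grade 1 changes no lapatinib dose. It is worth correcting only because the same row is being edited anyway.

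**Conclusion.** The point holds as a minor safety inconsistency. For Grade 1 diarrhoea with a complicating feature that no other Table 7 row would hold, section 3.5.3 requires a hold and a call to the monitor, and Table 7 prescribes neither. This rests on the wording alone.

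Three stronger conclusions might be inferred, and the documents support none of them.

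- *The two sections conflict on dosing throughout.* They do not: both hold at Grade 3 and above, complicated Grade 2 is broadly compatible, and dosing for uncomplicated Grade 1 is the same.
- *About 11 of 20 patients, or a share given by the dehydration SAEs, are exposed to conflicting dosing instructions.* The first figure counts all related diarrhoea and the second counts serious reports. Neither measures the affected group, whose frequency cannot be derived.
- *A study result is compromised.* No sample size, endpoint or analysis depends on this point.

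**What to change.** In the Table 7 diarrhoea block, add a row: Grade 1-2 with any complicating feature listed in section 3.5.3 - hold lapatinib and discuss with the medical monitor. State that this row prevails over the by-grade default, and cross-refer section 3.5.3 and Table 7 to each other.

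In the same edit:

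- Replace the Grade 1 management entry in Table 7 with the section 3.5.3 supportive measures (diet, fluids, loperamide).
- Align the Grade 2 text. Either section 3.5.3 defers to Table 7's sequence (restart at the same dose, reduce on recurrence or if unacceptable to the patient), or Table 7 admits an earlier reduction. The choice matters because section 3.6.1 permits only one reduction per subject.

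The cost is one table row, two cross-references and two matched wordings in a protocol amendment. No visits, procedures or analyses are added.
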